## Abstract

**Background:**

People struggling with chronic pain may benefit from different types of non-pharmacological interventions such as self-management courses. Self-management courses aim to increase participants’ skills and knowledge in managing chronic conditions. Community health-care services in Norway have increasingly established Healthy Life Centres (HLCs) to offer easily accessible interventions to people in need of support to better handle a life with chronic illness. The aim of this trial is to investigate the expectations, effect and experience of an easily accessible, group-based self-management course delivered at a HLC for people with chronic pain.

**Methods/Design:**

This is an open pragmatic two-armed randomised controlled trial with an embedded qualitative study. The intervention is a self-management course comprising education, discussions, exchange of experiences between the participants, and physical movement exercises. The control group is offered a drop-in outdoor physical activity. The intervention period is 6 weeks. The primary outcome is patient activation measured by the patient activation measure (PAM). The secondary outcomes include measures of self-efficacy, pain and quality of life. Data will be collected at baseline, and after 3, 6 and 12 months. Using a mixed linear model, the number needed in each arm to achieve a power of 80 % becomes 55. To allow for dropout, the aim is to include 120 participants. Analysis will be done using mixed linear models. In the embedded qualitative study, we will perform semi-structured face-to-face interviews with a sample from both trial arms before randomisation and after 3 and 12 months. The topics elaborated will be motivation for participation and experiences with the activity related to possible changes in managing and coping with chronic pain.

**Discussion:**

There is need for more knowledge on interventions delivering self-care support in an easily accessible way that aim to reach those in need of this kind of health service. This trial will produce important knowledge on the effect and the experiences of participants in such an easily accessible self-management course delivered in Norwegian public primary care.

**Trial registration:**

ClinicalTrials.gov: NCT02531282. Registered on 21 August 2015.

**Electronic supplementary material:**

The online version of this article (doi:10.1186/s13063-016-1462-6) contains supplementary material, which is available to authorized users.

## Background

The rising prevalence in long-term conditions (LTCs) presents a major challenge in society and health-care services worldwide [1, 2]. This has led to increased attention towards interventions supporting self-care as effective approaches and core components in the health-care service [3, 4].

Self-care indicates the actions people take independently to lead a healthy lifestyle and how they engage in behaviours that affect their health [3, 5, 6]. To take on the responsibility that lies within self-care, people need knowledge and skills on how to manage their own health, highlighting the importance of being active and engaged as patients [6, 7]. This can be seen as an ideological shift from patients as passive recipients of treatment to patients being empowered individuals managing their own health [8]. Although people manage their health mostly outside the health-care services, people with LTCs typically need ongoing treatment over decades. They may therefore benefit at varying times from interventions supporting self-care [6, 7].

This benefit has led to an increase in interventions to support self-care, typically called self-care support or self-management interventions [6, 9]. In the following, we will use the term self-management interventions when referring to these activities. Self-management interventions are offered in various forms. They can be led by lay persons or professionals, be generic or disease specific, and be delivered in groups or to individuals [5, 9]. They have been shown to result in improvements in various domains such as in the participants’ engagement, self-efficacy, mood, physical symptoms and function, and reduced health-service utilisation [4, 7, 10].

However, reaching and engaging those likely to benefit from participation in self-management interventions have been described as insufficient, leading to high attrition rates and low uptake [11, 12]. Difficulties in accessing health services and health-care personnel are described by patients as barriers to participation in different types of self-management interventions [13–15]. As self-care support is acknowledged as a key in management of LTCs, a sustainable number of resources has been invested in offering these interventions [6, 16]. Delivering easily accessible self-management interventions, therefore, seems to be significant in providing a sustainable health service, and primary care and community health-care services seem to be the suitable arenas for them [12].

In a Norwegian context, group-based patient education as a self-management activity has traditionally been offered in hospitals (see general introduction in [17]). Recent health reforms promote support for self-care to be carried out also in the local communities [18]. This action aims to offer interventions that are easy to access. In addition, the Norwegian Directorate of Health has since 2004 encouraged municipalities to establish Healthy Life Centres (HLCs) as part of their public health care [19]. HLCs are low-threshold health-care services delivering easily accessible activities and interventions in the communities. These services aim to support people at risk with health behavioural changes and in managing chronic conditions [19, 20]. The government writes that the theoretical framework of HLCs’ interventions should be in salutogenesis [20], where strengthening people’s capacities to use their own and available health resources is central [21].

One group utilising HLCs comprises people with long-lasting pain. Long-lasting or chronic pain is a widespread LTC that affects up to one-third of the population [22–24]. The condition affects the physical, social and psychological dimensions in life [25–27]. Pain sufferers often describe problems of sleeplessness, depression, poor quality of life, and exhaustion, as well as interference with physical ability, social relations and work life [23, 28, 29]. An increase in the number of people struggling with chronic pain is documented [22, 23]. It has an impact on society in terms of increased health-care utilisation, sick leave and early retirement [1, 23, 30].

As chronic pain has an impact on many aspects in a person’s life, different treatment approaches are needed. Current recommendations focus on both pharmacological and non-pharmacological interventions [27, 31]. One central approach in non-pharmacological interventions is support for self-management, aiming to increase the individual’s ability to manage his or her pain in everyday life. Because today’s treatments provide modest improvement in pain and minimum improvements in physical and emotional functioning [27, 32], a substantial number of people are left to struggle with chronic pain in everyday life. This difficulty pinpoints the importance of communities addressing the need for health care for this group of people, preferably by delivering easily accessible interventions, like the ones offered in the Norwegian HLCs. However, to our knowledge, nothing has been published on the effect of and on participant experiences with self-management interventions addressing chronic pain that are delivered in a HLC.

### Aims and objectives

This trial’s overall aim is to investigate the expectations, effect and experiences of an easily accessible self-management course for people with chronic pain delivered at a HLC in community public health care.

The primary objective is to study in a randomised controlled trial (RCT) the hypothesis that an easily accessible group-based self-management course for people with chronic pain is more effective at patient activation than a drop-in group-based easy outdoor physical activity.

The embedded qualitative study seeks to investigate the expectations for participation in a self-management course in this setting. In addition, we will investigate the participants’ experiences with the intervention and changes in how they manage their lives with chronic pain.

## Methods/Design

This is an open pragmatic parallel two-arm RCT with an embedded qualitative study (Fig 1). The intervention is complex, as it comprises multiple interacting components [33, 34]. The Medical Research Council guidelines for complex interventions [34] and the SPIRIT guideline (Standard Protocol Items: Recommendations for Interventional Trials) with its checklist [35] were consulted when writing the protocol.

**Fig. 1 Fig1:**
[figure not shown]
Flow chart of the trial

### Setting

HLCs (“Frisklivssentral” in Norwegian) are a public service offered by municipalities as part of the Norwegian community health-care system [19]. The HLCs strive to offer easily accessible interventions with few barriers for participation. They aim to give a low-threshold health-care service that people can attend with or without referral from others. In addition, a HLC receives referrals from general practitioners, physiotherapists and the Norwegian Labour and Welfare Administration [20].

Our project is situated at a HLC in a city in central Norway serving a population of approximately 185,000 inhabitants. The centre has 5.5 positions occupied by multidisciplinary health professionals with a bachelor’s or master’s degree. The HLC offers several group-based activities and interventions, e.g. indoor and outdoor physical activity, healthy diet courses, smoking cessation programmes and courses focusing on coping with depression or anhedonia. The drop-in physical activity offered to the control group is an example of an activity at the HLC where people can attend without referral or further commitment. In cooperation with patient organisations, the HLC staff developed the self-management course constituting the intervention arm in this trial.

### Inclusion criteria

The inclusion criteria are adults of 18 years or older who can self-report challenges with pain for more than 3 months and are able to take part in group discussions in Norwegian. The 3-month criterion is set according to the International Association for the Study of Pain definition of chronic pain as being ‘pain without apparent biological value that has persisted beyond the normal tissue healing time over 3 months’ [36–38]. To enhance external validity, the inclusion criteria are simple and broad, as in similar pragmatic trials [32, 38] and because they mirror practice at the HLC.

### Exclusion criteria

The exclusion criteria are not being able to take part in the activity offered to the control group (1 hour of easy physical activity, e.g. walking), chronic pain arising from malignant diseases, and not having the capacity to consent and participate.

### Recruitment

Information on the opportunity to refer people to the trial will be given to physiotherapists, general practitioners, Norwegian Labour and Welfare Administration and other important organisations in the municipality. To promote the possibility of self-referral, flyers and posters with information on the trial will also be distributed to offices and waiting areas of general practitioners and physiotherapists, and to Norwegian Labour and Welfare Administration offices. Advertisements will be placed in newspapers, on social media and websites, as well as in emails to relevant patient organisations.

The first author will be responsible for checking the participants’ eligibility criteria before enrolment. Participants will be enrolled until the target sample size is reached.

Recruitment to RCTs is acknowledged as challenging [10]. To make participation in the trial more appealing, all participants are offered an activity. Amounts normally paid for attending interventions in the HLC (normally about $34/€31) will be covered by the trial. No other financial support is planned.

### Interventions

#### Self-management course

The content of the self-management course includes theoretical education, group discussions based on the theoretical input, sharing of experiences and movement exercises. The staff developed the course based on recommendations found in the literature (e.g. [39–41]) and added elements from cognitive behavioural therapy focusing on the participants’ thoughts, emotions and actions. The theoretical part of the course comprises pain theory, barriers in everyday life due to chronic pain, problem-solving, goal-setting and techniques to deal with fatigue, poor sleep, frustrations and isolation. The movement exercises in each session aim to improve balance, posture and breathing, providing the participants with techniques to increase body awareness and the ability to relax. These techniques are essential in Norwegian psychomotor physiotherapy [42] on which this element of the course is built.

Guidelines for how to carry out the course have been developed to help the instructors, ensuring all groups are offered the same content and material (see Additional file 1).

The course is delivered as 2.5-hour weekly group workshops during the daytime for a period of 6 weeks, reaching a total of 15 hours, with 8–10 participants in each group. Two employees who have been dedicated to facilitating the course have a professional background as physiotherapists. All workshops start with the theoretical elements followed by the part of the course introducing movement exercises in a training room. Between the parts, there will be breaks for social interaction. Between each workshop, the participants will be given homework, e.g. working on their goal-setting plan.

#### Control group

Participants in the control group will be offered a drop-in outdoor easy physical activity, comprising walking and simple strength exercises. The activity will be adjusted to the participants’ physical ability, to keep it both easily accessible and rewarding. The rationale for choosing this activity is that the HLC already offers this activity as a drop-in service without registration or further commitment from people. Offering an activity to all participants in the trial is recognised as ethical and it is good clinical practice [43, 44]. Participation in the control group activity is voluntary, in line with the drop-in policy at the HLC.

The easy physical activity will be delivered as a weekly 1-hour session for a period of 6 weeks. The activity will be in groups with a group size similar to the intervention (8–10 participants in each group) and led by two instructors with skills in physical activity. The group will meet outdoors on a trail popular for walking among the municipality’s inhabitants. However, due to changing weather conditions and according to conditions on the trail, the location might be changed to another area during winter.

### Documentation of the delivery of the intervention

To document the delivery of the interventions, the instructors will complete an evaluation form for each group. They will be asked to report their experiences with the delivery, the group dynamics and whether there were any adverse events. The instructors will also report the number of participants attending each session.

### Randomisation and allocation

Randomisation to the intervention or control group will be done using a computerised Internet-based randomisation service. Previous studies on interventions in primary care indicate that more women than men participate in self-management interventions [45]. Thus, the randomisation will stratify on gender allocating men equally to both trial arms.

The first author will inform the participants of the result of the allocation by telephone or email immediately after the randomisation. After allocation to one of the trial arms, the participants are informed that there will be no possibility of changing arms.

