### Methodology for the RCT

#### Data collection

Data will be collected through self-report questionnaires at baseline (*t*_0_), and after 3 (*t*_1_), 6 (*t*_2_) and 12 months (*t*_3_). At baseline, the first author will be available for questions when the participants fill in the questionnaire. The first author will also supervise the physical ability test at baseline. Background variables such as age, gender, marital status, employment status, pain duration, referring institution, other diseases coded with the International Classification of Primary Care 2 (ICPC-2) [47], current medication and health-care utilisation will also be collected at baseline. At the three follow-up points (3, 6 and 12 months), the participants will be sent the questionnaires by mail. The participants will bring the completed self-administrated questionnaires to the follow-up visits, where a research assistant will supervise the physical ability test. There will be one postal reminder for each follow-up data collection point, and non-responders will be contacted by phone or email allowing a delay of up to 4 weeks.

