
#### Sample size

The translation of PAM into different languages has provided mean values for PAM in different populations [55, 83–85]. However, there is no common cut-off level for a clinically relevant change in PAM [86], and improvements in a PAM score after an intervention vary from 3 to 8 points [standard deviation (SD) 12–17] in different studies [54, 87–89]. Using a mixed linear model assuming a correlation within participants of 0.5, a difference between the groups at 12 months of 6 points, a SD of 13 [54], and a power of 80 %, the number needed in each arm becomes 55. To allow for dropout, the aim is to include 120 participants.

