#### Statistical analysis

Outcome analyses will be conducted according to an intention-to-treat principle with mixed linear models. A mixed model accounts for repeated measures and potentially uses more of the data compared with an analysis of covariance. To account for within-subject correlations, participant ID will be specified as a random effect. The effect of intervention and time will be specified as a fixed effect with the levels ‘baseline’, ‘active 3 months’, ‘control 3 months’, ‘active 6 months’, ‘control 6 months’, ‘active 12 months’ and ‘control 12 months’.

In addition, a per-protocol analysis will be conducted, including participants who have been present at a minimum of three group sessions.

The confidence level is set to 95 %, and *p* ≤ 0.05 will be considered statistically significant. We will use Stata 14 [90], IBM SPSS 23 [91] and R version 2.13.1 [92] to analyse the data. A statistician blinded to group allocation will supervise the analysis.

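### Randomisation is stratified by gender, but the published outcome model has no gender term; if gender predicts the outcome, the test is slightly conservative

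*Protocol article*

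**What the plan says.** In the protocol article, Randomisation and allocation, gender is the only stratification factor: "the randomisation will stratify on gender allocating men equally to both trial arms". The reason given is that "more women than men participate in self-management interventions". Nothing is said about gender predicting patient activation.

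The Statistical analysis section then describes the mixed model. For the random part, "participant ID will be specified as a random effect". For the fixed part, "The effect of intervention and time will be specified as a fixed effect with the levels", followed by seven levels: one baseline level shared by both arms, and an active and a control level at each of 3, 6 and 12 months. No gender term or other covariate is named.

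Gender is available: Data collection lists "Background variables such as age, gender, marital status, employment status, pain duration" among the items recorded at baseline.

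**The concern.** Stratifying balances gender between the arms, so differences between men and women largely cancel out of the treatment contrast. A model without gender does not know this. It leaves the between-gender variance in its estimated standard error. If gender is prognostic, the confidence intervals are then somewhat wider than the design warrants and the real test level falls below 5%.

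What is at stake is a little precision, not validity. The treatment estimate is unbiased either way, and the error runs in the cautious direction.

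**Working it through.** **Inputs from the article (Sample size):** SD 13; "assuming a correlation within participants of 0.5"; "a difference between the groups at 12 months of 6 points"; power 80%; and "the number needed in each arm becomes 55". A two-sided 5% test is assumed.

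**Assumed, because the article does not give them:** 20–30% men; a gender difference in PAM of 0 to 0.8 SD; men and women each split evenly between the arms.

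**1. Reproduce the plan's figure.** With a shared baseline and correlation ρ = 0.5, the residual variance at 12 months is 169 × (1 − 0.25) = 126.75. Then n = 2 × [13 × (1.960 + 0.842)/6]² × 0.75 = 73.69 × 0.75 = 55.27 per arm, which matches 55. Power at 55 per arm is 79.8%. Gender plays no part in this calculation.

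**2. Standard error of the stated model.** √(2 × 126.75/55) = 2.147. Generalised least squares for the seven-level model with four time points gives the same value.

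**3. True standard error under gender-balanced allocation.** Let p be the share of men and d the gender difference in SD units. Gender then accounts for R = p(1 − p)d² of the total variance. The model in effect compares the 12-month score minus ρ times the baseline score. A constant gender difference is therefore halved before it reaches the contrast, and the variance that balancing removes is 169 × R × (1 − 0.5)². So:

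- true SE = √(2 × 169 × (0.75 − 0.25R)/55)
- real level = 2 × [1 − Φ(1.96 × 2.147/true SE)]

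For example, with 20% men and 0.5 SD, R = 0.16 × 0.25 = 0.04. The true SE is √(2 × 169 × 0.74/55) = 2.1325, and the excess is 2.1469/2.1325 − 1 = 0.67%.

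| Men | Difference | R | True SE | SE too large by | Real level | SE with gender in model | n per arm needed with gender |
|---|---|---|---|---|---|---|---|
| any | 0 | 0 | 2.147 | 0% | 5.0% | 2.147 | 55.3 |
| 20% | 0.3 SD | 0.0144 | 2.142 | 0.24% | 4.95% | 2.142 | 55.0 |
| 20% | 0.5 SD | 0.0400 | 2.133 | 0.67% | 4.85% | 2.132 | 54.5 |
| 20% | 0.8 SD | 0.1024 | 2.110 | 1.75% | 4.61% | 2.106 | 53.2 |
| 30% | 0.5 SD | 0.0525 | 2.128 | 0.89% | 4.80% | 2.127 | 54.3 |
| 30% | 0.8 SD | 0.1344 | 2.098 | 2.3% | 4.5% | 2.091 | 52.4 |

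Adding gender raises power by about 0.1 points (20% men, 0.3 SD), 0.4 points (20%, 0.5 SD) and 1.5 points (30%, 0.8 SD).

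**4. Sensitivity: gender affects follow-up but not baseline.** Baseline then absorbs nothing, and 0.25R becomes R. With 20% men the excess is 1.0% at 0.3 SD and 2.8% at 0.5 SD (real level 4.4%). With 30% men and 0.5 SD it is 3.7%. At 0.8 SD it would be 7.6% to 10.4%, but that needs a gap of 0.8 × 13 = 10.4 points to open after baseline where none existed before. This exceeds the 6-point treatment effect the trial is powered for.

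**The case against.** **The article is condensed.** The sentence on fixed effects can be read as explaining how the intervention-by-time effect is coded, not as a closed list of terms. An analysis plan that is not shown may include gender. This stands in part: nobody can say from the article that the final analysis will omit gender. But the article does more than name a class of model. It spells out the terms and levels, and the model so described does not reflect the stratification.

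**Gender may not matter for PAM.** This stands in full. The stated reason for stratifying is the expected shortage of men, not prognosis, and the design achieves its aim of splitting men evenly whatever the model contains. A reader might infer that the standard errors are necessarily too large, or that the stratification is wasted. The article supports neither.

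**The loss is easily overstated.** A reader might take a gender difference of 4–6 points beyond baseline PAM as ordinary. That gives 0.16 × 16/126.75 = 2.0% to 0.21 × 36/126.75 = 6.0% of the residual variance, and a 1–3% gain in SE. But at correlation 0.5, 4–6 points left after baseline means a raw constant difference of 8–12 points (0.6–0.9 SD), or a gap that appears only after baseline. For a raw constant difference of 4–6 points, 2–3 points remain. The share is then 0.16 × 4/126.75 = 0.5% to 0.21 × 9/126.75 = 1.5%, and the SE changes by about 0.25–0.75%. This objection stands too.

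**Secondary outcomes.** Gender might matter more for some of them, but the article gives no figure, so no larger loss can be claimed.

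**Conclusion.** The mismatch between the randomisation and the stated model is real, and its consequence is minor. It depends on gender being associated with the outcome, which the article does not say. For PAM at 12 months, with 20–30% men and a constant gender difference of 0 to 0.8 SD, the standard error is too large by 0% to about 2.3% and the real level is 5.0% to about 4.5%. Up to 0.5 SD the excess is under 1%. An excess of about 3% or more is reached only if gender affects follow-up scores well beyond what baseline shows.

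These figures assume the article's SD of 13, its correlation of 0.5, 55 per arm, and allocation balanced within gender. The trial's conclusion is unlikely to turn on this. Severity is low.

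**What to change.** Add gender as a fixed effect to the primary mixed model, and to the same model for each secondary outcome. A single gender term assumes a constant difference over time. If that is doubted, specify a gender-by-time term as well, before the data are analysed. If a fuller analysis plan already includes gender, it is enough to say so.

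The cost is one model term. Gender is already recorded at baseline, no new data are needed, and the target of 55 per arm (120 in total) stays as it is. Fixing the term in advance also avoids a discretionary choice of covariate later.
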